### Sample size

2.4

The sample size will be determined according to the difference test formula of the mean comparison between 2 groups (Power = 80%, *P* = .05). In this study, the Fried phenotype and SPPB will be taken as the main endpoints. According to previous studies, a sample of 250 (125 per group) is required to detect a 33% increment in the mean number of frailty criteria (from 1.2 to 1.6),^[13]^ a sample of 256 (128 per group) is required to detect a 41% between-group difference in the average reduction in the number of frailty criteria (from 0.41 to 0.8),^[12]^ and a sample of 202 (101 per group) is required to detect a 1.44-points between-group difference in average increment on the 12-point SPPB scale (from −0.98 to 0.52).^[12]^ With an attrition rate of 15%, at least 320 participants (160 per group) will be recruited.

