Statistical analyses: We will conduct an intention-to-treat (ITT) analysis for the primary analysis, including primary and secondary outcomes, with a per-protocol (PP) analysis used for the sensitivity analysis. The ITT population is defined as all randomized participants in the study, and the PP population is defined as all randomized participants who were actually compliant with their treatment. The participants clinical features will be compared between the intervention and control groups. Continuous variables will be expressed as the mean ± standard deviation in a normal distribution and median and interquartile range in a non-normal distribution, and categorical variables will be expressed as numbers and percentages. Baseline characteristics will be compared by χ^2^ tests or Fishers exact tests for categorical variables and *t*-tests or Wilcoxons rank sum tests for continuous variables. A covariance analysis will be used to analyze the Fried phenotype, SPPB and modified means of the 2 groups, taking the central effect of the test into account, and the 95% confidence interval (CI) of the difference between the 2 groups will be calculated. Only when the above 2 main indicators satisfy the statistical hypothesis (superior effect), can the hypothesis be considered valid. For time-event data, the Kaplan–Meier method will be used to estimate death, non-elective hospital readmission and fall events. A log rank test will be performed for the 2 groups. A Cox proportional-hazard regression model will be used to calculate the effect of potential risk factors on the events. We will summarize the number of enrollments and completion of each center, list the drop-outs, compare the total drop-out rate and list the reasons for termination in detail and compare the characteristics between those with missing outcome data and those who have completed follow-up. The safety evaluation table will be included to describe the number of adverse events and the incidence of adverse events, serious adverse events, adverse reactions and serious adverse reactions in the two groups. Statistical significance will be set at a 2-sided *P* value <.05.

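### The 80% power is per endpoint, but success requires both Fried and SPPB; power for that rule is about 74–82%, roughly 77% at moderate correlation

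*Protocol article*

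**What the plan says.** Section 2.4 (Sample size) states that "the Fried phenotype and SPPB will be taken as the main endpoints" and sizes them with a "difference test formula of the mean comparison between 2 groups (Power = 80" per cent), at a significance level of 0.05. It gives three separate calculations, each for a single endpoint:

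- Fried, first source: "a sample of 250 (125 per group) is required to detect a 33% increment in the mean number of frailty criteria (from 1.2 to 1.6").
- Fried, second source: "a sample of 256 (128 per group) is required to detect a 41% between-group difference in the average reduction in the number of frailty criteria". The end values given for this difference are 0.41 and 0.8.
- SPPB: "a sample of 202 (101 per group) is required to detect a 1.44-points between-group difference in average increment on the 12-point SPPB scale". The end values given for this difference are −0.98 and 0.52.

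It then allows for 15% attrition and recruits at least 320, or 160 per group.

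Section 2.8 (Statistical management and analyses) specifies a covariance analysis of both outcomes and sets the decision rule: "Only when the above 2 main indicators satisfy the statistical hypothesis (superior effect), can the hypothesis be considered valid". On the level it says: "Statistical significance will be set at a 2-sided *P* value <.05".

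The article gives no correlation between the two endpoints and no power for winning on both.

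**The concern.** When both endpoints must succeed, the relevant power is the probability that both tests are significant in the right direction. That probability cannot exceed the smaller of the two marginal powers, and it falls below it unless the two test statistics are very highly correlated. An 80% attached to each endpoint alone therefore does not carry over to the rule in section 2.8.

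The stake is how a failed overall result is read. A win on one endpoint and a miss on the other counts as failure. A reader who takes 80% from section 2.4 will put the chance of missing a real benefit at 20%. Under the both-must-win rule, with both assumed effects true, it could be somewhat higher. Only power is at issue: requiring both endpoints does not inflate the type I error.

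**Working it through.** **Inputs from the article.** Two-sided 0.05 and 80% power; 1:1 allocation; 128 per group (Fried, the larger basis) or 125 (the other basis); 101 per group (SPPB); 320 recruited; 15% attrition.

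**Assumptions.** The article states no standard deviations, so I take each stated n to give exactly 80% power. It states no correlation, so I show the range from 0 to 1. The correlation is oriented so that benefit on both measures is positive.

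**The plan's own figures.** With n per group = 2 × (1.960 + 0.8416)² × SD² / Δ², the stated sizes imply these SDs:

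| Endpoint | Δ | n per group | Implied SD |
|---|---|---|---|
| Fried, first source | 0.40 | 125 | 1.13 |
| Fried, second source | 0.39 | 128 | 1.11 |
| SPPB | 1.44 | 101 | 3.65 |

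The three sample sizes cannot be verified independently, because these SDs are solved from them. They cancel in what follows.

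**Attrition.** 256 / 0.85 = 301.2, so 302 would have covered the larger Fried figure. The 320 planned is 18 more. Evaluable: 320 × 0.85 = 272, or 136 per arm.

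**Marginal power at 136 per arm.** The expected z-statistic scales with the square root of n, starting from 1.960 + 0.8416 = 2.8016 at the stated n.

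- Fried: 2.8016 × √(136/128) = 2.888; Φ(2.888 − 1.960) = 82.3%. On the 125 basis it is 83.2%.
- SPPB: 2.8016 × √(136/101) = 3.251; Φ(3.251 − 1.960) = 90.2%.

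**Joint power at 136 per arm.** This is the bivariate normal probability that both statistics exceed 1.960, at correlation r. At r = 0 it is the product 0.8233 × 0.9016 = 0.742. At r = 1 it equals the smaller marginal power.

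| r | Fried basis 128 | Fried basis 125 |
|---|---|---|
| 0 | 74.2% | 75.0% |
| 0.3 | 75.8% | 76.6% |
| 0.5 | 77.2% | 77.9% |
| 0.7 | 78.9% | 79.6% |
| 0.8 | 80.0% | 80.7% |
| 1 | 82.3% | 83.2% |

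Joint power reaches 80% at r of about 0.8 on the 128 basis and about 0.74 on the 125 basis.

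**Sensitivity to the SPPB inputs.** 0.52 − (−0.98) = 1.50, not 1.44. The size of the effect on power depends on which difference goes with the SD actually used. Scaling the SPPB statistic by 1.44/1.50 or 1.50/1.44 gives these results on the 128 basis:

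| r | Scaled by 1.44/1.50 | Scaled by 1.50/1.44 |
|---|---|---|
| 0 | 72.2% | 76.0% |
| 0.5 | 75.6% | 78.5% |
| 0.8 | 78.8% | 80.8% |

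**Sensitivity to attrition.** With no loss at all (160 per arm, 128 basis), joint power is 83% at r = 0 and 88% at r = 1.

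**Size needed for 80% joint power (128 basis, 15% loss).** 152 evaluable per arm at r = 0 (358 recruited), 145 at r = 0.5 (342 recruited), 140 at r = 0.7 (330 recruited).

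**The case against.** Several counter-arguments carry weight.

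- **Shared content.** Section 2.1 lists slow walking among the Fried criteria and gait speed among the SPPB tests. Independence is therefore an unlikely floor, and the 74% should not be read as the expected value. This stands. But Fried also covers weight loss, exhaustion and low activity, so a correlation of 0.8 cannot be taken for granted either.
- **Surplus recruitment.** The plan recruits 18 more than 15% attrition requires, which absorbs part of the loss. This stands, and the 136-per-arm figures already credit it.
- **Covariance analysis.** Section 2.8 plans adjusted means, while section 2.4 uses a plain comparison of means. If the source SDs were unadjusted, covariates that removed about 6% of residual variance on both endpoints (1 − 136/145) would restore 80% joint power at r = 0.5; about 11% (1 − 136/152) would do so at r = 0. The article does not say how the SDs were obtained or what the adjustment would gain, so this remains a possibility without a figure.
- **No explicit claim of joint power.** Section 2.4 ties each n to one endpoint and never says that 80% applies to both together, and an article condenses its full protocol. That makes this less than an arithmetic error. It does not remove the point, because the article itself prints both the power and the success rule, and the one does not describe the other.

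A reader might go further and multiply 0.80 × 0.80 to get 64%, or conclude that the trial is badly underpowered and that its 80% is meaningless. The document does not support this. 136 evaluable per arm exceeds both stated per-group sizes, SPPB has about 90% power on its own, and the endpoints are very probably positively correlated. At correlations above about 0.8 the joint power does pass 80%.

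**Conclusion.** The point holds in a limited form. The stated 80% is per-endpoint power and is not the power of the rule in section 2.8. At 136 evaluable per arm, joint power is about 74% at correlation 0, 77% at 0.5 and 80% at 0.8, with a ceiling of 82% (83% on the 125-per-group Fried basis). The shortfall against 80% is about 6 points at worst, about 3 at moderate correlation, and nil near 0.8. With both assumed effects true, the chance of missing the overall claim is about 23% at correlation 0.5.

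These figures rest on the stated sample sizes giving exactly 80% power, which cannot be checked without SDs; on 15% attrition; and on no gain from covariate adjustment. The conflict in the SPPB difference moves the result by about 2 points at low correlation and does not change the conclusion. Severity is minor to moderate: the statement of power needs correcting, while the design, the tests and the decision rule can stay as they are.

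**What to change.** Keep N = 320, the requirement to win on both endpoints, and two-sided 0.05 for each endpoint without alpha adjustment. In section 2.4:

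1. State that 80% is power per endpoint, and add a sentence such as: *With 136 evaluable participants per arm, the power to show superiority on both primary endpoints is about 74–82% depending on the correlation between them (about 77% at 0.5), before any gain from covariate adjustment.*
2. Reconcile the SPPB difference (1.44 as stated, 1.50 from its own end values), state the SD used for each endpoint, and recompute the joint figure if the SPPB sample size changes.

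The cost is one paragraph in the protocol, carried into the statistical analysis plan, and a slightly less favourable power statement. No extra participants are needed. If the sponsor wanted 80% joint power at correlation 0.5 under the same assumptions, recruitment would rise from 320 to 342; the modest shortfall does not make that necessary.

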### Research method and procedures

2.5

#### Outline

2.5.1

In this study, 320 elderly participants ≥70 years old will be randomly divided into the intervention group and control group. The intervention group will be given a routine diagnosis and treatment, a CGA and multi-disciplinary management for 12 months, and the control group will be followed up for 12 months with routine management for basic diseases. A flowchart of the trial is shown in Figure 1.

**Figure 1 F1:**
[figure not shown]
Overview of the participant flow for assessing the effect of a CGA and multi-disciplinary management on geriatric frail patients in China. CGA: comprehensive geriatric assessment; TCM = traditional Chinese medicine.

#### Recruitment process

2.5.2

A schematic overview of the outcomes, measures and timeline is shown in Table 1. The researchers will recruit participants who meet the inclusion criteria and do not meet the exclusion criteria from Beijing Hospital, PLA General Hospital and Tsinghua Changgeng Hospital.

**Table 1 T1:** Schedule of enrollment, interventions, and assessments.

	Visit 1	Visit 2	Visit 3	Visit 4
Time (months ± days)	**0** ± **5**	**3** ± **14**	**6** ± **30**	**12** ± **30**
Consent	√			
Inclusion/Exclusion Criteria	√			
Randomization	√			
Clinical Evaluation				
Demographic data	√			
Medical history	√			
Physical examination	√	√	√	√
Related auxiliary examination (±days), including routine blood test (±7), blood biochemical (±7) D-dimer (±7), NT-pro-BNP (±7), 25-OH-VD3 (±7), hsCRP (±7), thyroid function (±30), echocardiogram (±30).	√		√	√
CGA^∗^	√	√	√	√
Multi-disciplinary Management^∗^	√	√	√	√
Primary Outcomes		√	√	√
Secondary Outcomes		√	√	√
Adverse Event	√	√	√	√

All participants will receive a clinical evaluation by a nurse. Data on sociodemographic characteristics will be collected, including age, sex, marital status, educational level, smoking and alcohol consumption, and living arrangement. The health condition will be assessed by recording the number of comorbidities, fall occurrences in the past, sleeping quality (Pittsburgh sleep quality index [PSQI]),^[41]^ functional status (BADL, instrumental activity of daily living [IADL]),^[42]^ simple nutritional status (diet, appetite, and calf girth), physical activity or exercise, results of a special physical examination, psychosocial components (mini-mental state examination [MMSE],^[43]^ hospital anxiety and depression scale [HADS-A]),^[44]^ geriatric depression scale [GDS-5 items]),^[45]^ and related auxiliary examination (Table 1).

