### Eligibility criteria

2.2

Inclusion criteria for recruitment: hospitalized and ≥70 years old; have a Fried phenotype ≥3; are living in Beijing for at least 1 year and able to participate in the follow-up of the study; are able to volunteer to participate and sign informed consent.

Exclusion criteria for recruitment: currently participating in other similar clinical trials; have been treated with regular (≥3 days per week) traditional Chinese medicine (TCM) or acupuncture or have received regular (≥3 days per week) nutritional supplements or received treatment at a rehabilitation facility within the last 3 months; have exercised regularly at moderate intensity over the past 3 months (maximum heart rate of 50% × (220 – age) during exercise);^[40]^ are unable to complete the SPPB (main result of the study); are unable to participate in and stick to exercise alone; will be residing in a hospital or care home, including community specialist nursing facilities, rehabilitation centers and intermediate care facilities in the coming year; have dementia or severe cognitive impairment; have other severe concomitant conditions impair the ability of the patient; have end-stage disease with a life expectancy <12 months; have any other conditions or events that researchers or therapists consider to be excluded.

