### Intervention

2.6

Participants in the intervention group will receive a CGA and receive 12 months multi-disciplinary management. Interventions will be carried out by a multi-disciplinary team (including physicians, nurses, nutritionists, rehabilitation physicians, pharmacists, TCM physicians). A brief CGA will be carried out by nurses during the three days of hospitalization, including evaluations of the following data: hearing impairment, visual impairment, masticatory disorder, risk of fall and imbalance, history of falls, urinary incontinence and fecal incontinence, chronic constipation, and chronic pain. The specialized CGA and interventions are as follows:

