
### Follow-up

2.7

Data will be collected from all participants at 4 points throughout the study: before the intervention and 3, 6, and 12 months after the enrollment. Brief telephone reviews will be conducted approximately 2 to 3 times per month for all participants to promote adherence to the intervention. Participants in both groups will receive at least 12 months of telephone follow-up after the completion of the assessment or intervention in order to assess the durability and sustainability of any influence identified once the intervention stops.

Participants in the intervention group will be defined as treatment-compliant if they complete at least 50% of the planned rehabilitation exercises and/or 50% of their planned nutrition guidance program and 50% of the acupoint massage prescribed by TCM within 12 months. Participants will be required to make records in the debilitating record book. The individual dietary plan, rehabilitation exercise instruction with pictures and safety information, medication instruction, diagram of acupoint massage and patient education manual will also be represented in the record book in order to increase patients compliance. Researchers will assess the actual completion through the above requirements at the end of the intervention.

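### Table 1 schedules the outcomes only from Visit 2, so no recorded control-arm baseline is scheduled for SPPB (co-primary), CFS, EQ-5D or NRS-2002

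*Protocol article*

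**What the plan says.** All references are to the protocol article.

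- **Section 2.5.2, Table 1** ("Schedule of enrollment, interventions, and assessments"): the rows "Primary Outcomes" and "Secondary Outcomes" have ticks at Visits 2, 3 and 4 and none at Visit 1.
- **Section 2.7** sets the collection times for both arms: "Data will be collected from all participants at 4 points throughout the study: before the intervention and 3, 6, and 12 months after the enrollment".
- **Section 2.4**: one calculation uses the between-group difference in mean reduction of frailty criteria (0.41 against 0.8, 128 per group). Another uses "a 1.44-points between-group difference in average increment on the 12-point SPPB scale" (101 per group).
- **Section 2.2**: patients must "have a Fried phenotype ≥3", and those who cannot complete the SPPB are excluded.
- **Section 2.5.2, text**: a nurse evaluates every participant. The listed content includes BADL and past falls, but not SPPB, CFS, EQ-5D or NRS-2002.
- **Section 2.5.3**: allocation is generated once that evaluation is finished and entered in the EDC. The staff who perform it are blinded.
- **Section 2.6**: "Participants in the intervention group will receive a CGA and receive 12 months multi-disciplinary management". SPPB appears under the rehabilitation assessment of this CGA, and the NRS-2002 score under the nutrition assessment.
- **Section 2.8**: Fried and SPPB are analysed by covariance analysis, "taking the central effect of the test into account". Both must show superiority for the trial hypothesis to stand.

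**The concern.** The table is the document a site works from. If it is followed literally, the pre-randomisation visit contains no outcome assessment, and the text elsewhere fills the gap for some outcomes only.

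The SPPB matters most. It is co-primary, the trial cannot succeed without it, and its sample size is expressed as a change. EQ-5D is next: section 2.8 names it as one of two bases for the QALYs, and an EQ-5D utility path needs a month-0 value. CFS and NRS-2002 are in the same position as ordinary secondary outcomes.

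An analysis plan can add a covariate later. It cannot supply a measurement that the schedule did not collect. Section 3.1 reports recruitment as ongoing, so each baseline missed is lost.

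**Working it through.** **Step 1. What is fixed before randomisation, outcome by outcome.**

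| Outcome | Pre-randomisation source in both arms | Described elsewhere |
|---|---|---|
| Fried | Yes: inclusion criterion (2.2) | – |
| BADL | Yes: common clinical evaluation (2.5.2) | – |
| SPPB | Ability to complete it is checked (2.2); no recorded score is stated | Within the intervention-arm CGA (2.6) |
| NRS-2002 | None stated | Within the intervention-arm CGA (2.6) |
| CFS | None stated | No baseline described |
| EQ-5D | None stated | No baseline described |
| Mortality, readmission, on-trial falls, expenses | Not applicable: they accrue after entry | – |

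The blank Visit 1 cells do not look like damage from text extraction, because neighbouring rows (for example physical examination and adverse events) do carry a Visit 1 tick.

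**Step 2. The plan's own figures.** No stated figure decides this point. The largest requirement in section 2.4 is 256. Inflated for 15% attrition, this gives 256 / 0.85 = 301.2, so 302. The planned 320 is larger (it equals 256 / 0.80), so there is no shortfall. The per-group sizes cannot be reproduced independently because no SD is given. They can only be inverted (two-sided 0.05, 80% power, 1.96 + 0.842 = 2.802):

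SD = δ × √(n/2) / 2.802

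- Fried: 0.39 × √64 / 2.802 = 1.11
- SPPB: 1.44 × √50.5 / 2.802 = 3.65

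The SPPB means in brackets differ by 0.52 − (−0.98) = 1.50, not 1.44. With 1.50 the implied SD is 3.81. Since δ/SD is unchanged, so is the power below.

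**Step 3. Illustration of what a baseline is worth.** Assumptions: these SDs are SDs of change, since the effects are stated as changes; completers per arm are 160 × 0.85 = 136; the correlation ρ between baseline and follow-up is 0.3, 0.5 or 0.7, a range that is not in the document.

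- SD of follow-up values = SD of change / √(2(1 − ρ))
- Residual SD with baseline adjustment = SD of follow-up × √(1 − ρ²) = SD of change × √((1 + ρ)/2)
- Power = Φ(δ / (SD × √(2/136)) − 1.96)

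Example, SPPB at ρ = 0.7: the follow-up SD is 3.653 / √0.6 = 4.716, and 1.44 / (4.716 × 0.1213) − 1.96 = 0.56, giving 71.2%. With adjustment the SD is 3.653 × √0.85 = 3.368, and 1.44 / (3.368 × 0.1213) − 1.96 = 1.57, giving 94.1%.

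| Power at 136 per arm | ρ = 0.3 | ρ = 0.5 | ρ = 0.7 |
|---|---|---|---|
| Fried, follow-up values only | 92.7% | 82.3% | 60.9% |
| Fried, change score | 82.3% | 82.3% | 82.3% |
| Fried, baseline-adjusted | 94.8% | 91.5% | 87.9% |
| SPPB, follow-up values only | 97.0% | 90.2% | 71.2% |
| SPPB, change score | 90.2% | 90.2% | 90.2% |
| SPPB, baseline-adjusted | 98.1% | 96.4% | 94.1% |

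Baseline adjustment gives the highest power in every column.

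**The case against.** The strongest reply is that the outcome rows may be meant for post-baseline visits only, with baseline measures listed elsewhere. Section 2.7 speaks of data in general and does not name the outcomes, and Table 1 does collect other data at Visit 1. That stands: the conflict with section 2.7 is by implication. It does not close the gap, because for four outcomes nothing is listed elsewhere for controls.

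A reader might infer more than the document supports, in four ways.

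- *That no outcome has a comparable baseline in the two arms.* This is wrong for Fried, which everyone must meet at entry, and for BADL, which is in the common blinded evaluation.
- *That SPPB is never measured in controls before randomisation.* The eligibility check implies that it is at least attempted in everyone, and the special physical examination recorded for all participants has unspecified content. The CGA row in Table 1 carries an asterisk whose footnote is not in the text at hand. What is missing is a scheduled, recorded score; absence is not proven.
- *That different staff reading the baseline SPPB in the two arms would bias the result by some amount.* Section 2.6 does not say who scores the SPPB within the CGA or when, and nothing in the document gives a rating difference. No bias can be quantified.
- *That naming only centre in section 2.8 is an error.* A covariance analysis usually carries a further covariate, and the full list may sit in an analysis plan that is not shown. Naming the baseline is a worthwhile clarification, not the correction of a mistake.

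**Conclusion.** The point holds in a limited form. Table 1 as printed schedules no outcome at Visit 1. That fits poorly with pre-intervention data collection in section 2.7 and with the change-based sizing in section 2.4. For SPPB, CFS, EQ-5D and NRS-2002, no recorded control-arm baseline is scheduled anywhere in the article.

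The size depends on quantities the document does not give. Under the stated assumptions, an SPPB analysis from follow-up values alone has between 97% and 71% power as ρ rises from 0.3 to 0.7, against 98% to 94% with adjustment. The Fried figures (93% to 61%, against 95% to 88%) show only the value of using a baseline that is already available. Because entry requires at least three of five criteria, the baseline range of Fried is narrow, and this may hold its correlation down.

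These figures do not show that the trial is underpowered. If change is measured and analysed, power under the same assumptions is 82% for Fried and 90% for SPPB. The matter should be corrected because it concerns a co-primary outcome and a missed baseline cannot be recovered.

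**What to change.** In Table 1, tick Visit 1 for Fried, SPPB, CFS, BADL, EQ-5D and NRS-2002. Leave mortality, readmission, on-trial falls and insurance expenses unticked there, since they accrue only after entry; this means splitting the secondary outcomes row. State in section 2.5.2 that these six are scored in both arms by the blinded evaluation staff before randomisation, with the SPPB score recorded and not only the ability to complete the test. Add one clause to section 2.8: the covariance analysis of Fried and of SPPB includes that outcome's baseline value together with centre.

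The cost is a table correction, two sentences and a few extra minutes of assessment per control patient. Fried is already assessed and SPPB at least attempted at eligibility, and BADL is already in the common evaluation, so the added scales are CFS, EQ-5D and NRS-2002. For patients already enrolled, check whether the SPPB score from the eligibility check was kept.
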